#### Baseline, Posttest, and Follow-Up Assessments

On the day each wave is due to begin, participants receive an email (and optional SMS) inviting them to complete the baseline survey. The survey is accessible for 7 days, and participants who do not complete it are automatically withdrawn. This process is repeated for the 10-week and 22-week assessments. All participants receive 2 email reminders (and 2 optional SMS reminders) for the survey completions.

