### Hypotheses

The primary hypothesis is that educators who are allocated to receive the BEAM program will report significantly higher levels of confidence at posttest (primary endpoint) when compared with the waitlist control condition and that these effects will be sustained at follow-up. It is also hypothesized that educators who receive the BEAM program will report greater improvements in mental health knowledge, stigma, and psychological distress at posttest and a greater frequency of helping behaviors at follow-up, when compared with those in the control condition.

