#### Withdrawal of Consent

Participants can withdraw consent at any time without providing a reason by contacting the research team, replying to any email communication with the word *withdraw*, or completing the withdrawal form located within the PISCF. When a participant withdraws, all study data are retained, but no further data are collected, and all study communication ceases.

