### Control Condition

This study uses a waitlist control condition. Participants in the control condition will receive access to the intervention at no cost immediately after they complete the follow-up survey (22 weeks post baseline). If they do not complete the follow-up survey, they will receive access immediately after the survey has closed. They will receive access to the full program whether they have not completed the survey or not.

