#### Statistical Methods

The primary analysis will use a mixed model repeated measures analysis of variance (MMRM), accounting for repeated assessments within individuals and a random effect to account for clustering within schools. Models will include the factors time, condition (intervention vs control), and their interaction, with the critical test of effectiveness being planned contrasts of this interaction from baseline to postintervention (the trial primary endpoint) and follow-up (secondary endpoint). An unconstrained variance-covariance matrix will be used to accommodate within-participant effects. The method of Kenward and Roger [38] will be used to estimate the degrees of freedom for tests of all effects. Any baseline variables identified as substantially imbalanced between groups will be added to the models on an exploratory basis to confirm the robustness of the findings to this imbalance. Where distributional assumptions cannot be satisfied, bootstrapping methods or generalized mixed models (eg, binary MMRM) may be used to confirm the robustness of the findings. MMRM constitutes an intention-to-treat analysis, as it includes all available data under the missing-at-random assumption. Between-group effect sizes will be estimated using the estimated model means and variances.

Secondary and additional outcome analyses will involve contrasts comparing changes from baseline to follow-up analyses of secondary outcomes (mental health knowledge, stigma, helping behaviors, and psychological distress) from baseline to other occasions of measurement, using an MMRM approach, as described above. If the intervention is found to be effective, exploratory analyses will examine evidence for moderation effects, that is, whether the intervention was more effective for certain subgroups of the sample. This may include teacher attributes such as gender or age and school characteristics such as ICSEA status.

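### As written, missing the 10-week survey window means automatic withdrawal, which, read with the withdrawal section, costs the 22-week outcome of participants who never asked to leave

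*Protocol article*

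**What the plan says.** Under Baseline, Posttest, and Follow-Up Assessments, the baseline procedure is an emailed invitation (with optional SMS) and a limited window: "The survey is accessible for 7 days". The text continues that "participants who do not complete it are automatically withdrawn. This process is repeated for the 10-week and 22-week assessments". No exception is made for the posttest.

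Under Withdrawal of Consent, the article gives the consequence: "When a participant withdraws, all study data are retained, but no further data are collected, and all study communication ceases". The routes listed there are all started by the participant (contacting the team, replying to an email, or completing a form).

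Under Control Condition, controls who miss the 22-week survey are still provided for: "If they do not complete the follow-up survey, they will receive access immediately after the survey has closed". A missed 10-week survey is not mentioned.

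Under Statistical Methods, the contrast from baseline to posttest is the primary endpoint and the contrast to follow-up the secondary one. The analysis is described thus: "MMRM constitutes an intention-to-treat analysis, as it includes all available data under the missing-at-random assumption". Under Hypotheses, the confidence effect is expected to be sustained at follow-up, and the intervention arm is expected to report "a greater frequency of helping behaviors at follow-up".

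**The concern.** A missed survey and a withdrawal are different events. Someone who was too busy in one particular week has not withdrawn consent and may well answer 12 weeks later. The article uses one word for both events and attaches only one set of consequences to it. Followed literally, the procedure turns a single missed posttest into permanent loss to follow-up.

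What is at stake is chiefly the 22-week data, on which the durability of the confidence effect and the helping-behavior hypothesis rest. There is also a smaller, indirect cost at posttest. The planned mixed model has an unconstrained covariance matrix, so a participant with baseline and week-22 values but no posttest value still contributes some information to the posttest contrast. That information is lost if the week-22 survey is never sent.

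Missed windows are foreseeable in this population: the Introduction reports that lack of time and forgetfulness hampered program completion in the pilot.

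**Working it through.** **1. The plan's own sample size, reproduced.** Inputs from Sample Size: effect 0.50 SD, two-sided alpha 0.05, power 80%, 5 educators per school, intraclass correlation 0.07, attrition 30%.

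- Individually randomized, t-test: 63.8, so 64 per arm.
- Design effect: 1 + (5 − 1) × 0.07 = 1.28.
- 64 × 1.28 = 81.9, so 82 per arm, or 164 analysable in total.
- 82 / 0.70 = 117.1, stated as 117 per arm; 2 × 117 = 234; 234 / 5 = 46.8, so 47 schools.

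The stated figures hold. No figure in the article is disputed here.

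**2. The sections side by side.**

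| Event | Assessments section | Withdrawal section | Control Condition section |
|---|---|---|---|
| Misses 10-week survey | Withdrawn, if the repeated process includes that clause | No further data or contact, if it applies to automatic withdrawal | Silent |
| Misses 22-week survey | Withdrawn, on the same reading | No further contact, on the same reading | Control still receives program access |

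The first row produces the loss at week 22. In the second row the sections cannot all hold as written.

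**3. Outcomes lost through the rule alone.** The article gives neither the share who miss the posttest nor the share of those who would answer later, so both are assumed. Enrolled with completed baseline: 295 (Results section).

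- Low: 295 × 0.20 × 1/3 = 20; 20 / 295 = 7%.
- High: 295 × 0.30 × 1/2 = 44; 44 / 295 = 15%.

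**4. Total loss at week 22.** Let m1 be the share missing the posttest, m2 the share of the rest missing follow-up, and r the share of posttest missers who would answer at week 22 if invited.

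- Rule applied: loss = 1 − (1 − m1)(1 − m2).
- Still invited: loss = 1 − (1 − m1)(1 − m2) − m1 × r.
- Power for 0.50 SD: normal approximation with n / 2 / 1.28 effective participants per arm. This is a simple two-group comparison, for illustration.

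| Enrolled | m1 | m2 | Rule applied: n (loss), power | Still invited, r = 25% to 50%: n (loss), power |
|---|---|---|---|---|
| 295 | 20% | 10% | 212 (28%), 0.896 | 227 to 242 (23% to 18%), 0.915 to 0.930 |
| 295 | 30% | 10% | 186 (37%), 0.854 | 208 to 230 (29.5% to 22%), 0.890 to 0.918 |
| 295 | 30% | 20% | 165 (44%), 0.811 | 187 to 209 (36.5% to 29%), 0.856 to 0.892 |
| 234 | 30% | 10% | 147 (37%), 0.765 | 165 to 183 (29.5% to 22%), 0.810 to 0.847 |

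With the 295 enrolled, even the worst row leaves 165, just above the 164 required. At the target of 234, the 30% / 10% case would have fallen short of 164 under the rule and would have met it had posttest missers still been invited.

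**The case against.** The strongest reply is that the loss is inferred, not stated. Two steps are needed: the repeated process must include the withdrawal clause and not only the invitation and 7-day window, and automatic withdrawal must carry the consequences listed under Withdrawal of Consent. The first step is the natural reading, because the withdrawal clause comes immediately before. The second is weaker. That section opens with "Participants can withdraw consent at any time without providing a reason" and describes only what participants themselves initiate. The Control Condition section also counts against the harsh reading, since a control who misses the 22-week survey still receives program access. This stands as a reason for moderate confidence. It does not remove the point: no other meaning of withdrawn is given, and nowhere are posttest non-completers said to be invited at week 22.

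A reader might infer more than the documents support:

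- **That the primary endpoint is compromised.** A rule triggered by a missed posttest deletes no posttest value. The loss to that contrast is indirect and not quantified here.
- **That the rule breaks the missing-at-random assumption or the intention-to-treat claim.** Monotone missingness does not violate that assumption, which turns on why the posttest was missed, rule or no rule. Data already collected are kept and analysed.
- **That the loss differs by arm.** The Limitations remark that the 22-week wait may affect attrition does not address missing the week-10 survey. A difference between arms at that point is speculation.
- **That the trial is underpowered.** With 295 enrolled, the assumed ranges above do not show this.

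**Conclusion.** The point holds as an avoidable loss of secondary-endpoint data and an inconsistency between three sections. As written, a participant who misses the posttest without asking to leave would not be surveyed at week 22. The cost is about 20 to 44 outcomes of 295 (7% to 15%), which rests entirely on assumed rates: 20% to 30% missing the posttest, and one third to one half of those willing to answer later. Enrolment above target absorbs much of the effect on power, but the outcomes are still lost for no gain. This should be fixed, and confidence is moderate because the result depends on applying the consent-withdrawal consequences to automatic withdrawal. It does not invalidate the primary analysis.

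**What to change.** - Limit automatic withdrawal to non-completion of the baseline survey.
- State that a missed 10-week survey is a missed assessment: every participant who has not withdrawn consent is invited to the 22-week survey, and all available outcomes enter the mixed model.
- Keep the term withdrawn, after baseline, for participants who ask to leave.
- Reconcile the Assessments, Withdrawal of Consent and Control Condition sections, so that the position of a participant who misses either later survey, including a control's program access, is stated once and consistently.
- Apply this to follow-up invitations still to be sent. The Results section says intervention participants are still using the program, with follow-up due to finish in March 2021.

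The cost is a platform setting, a sentence or two of text, a few more emails, and a gift voucher of Aus $15 for each additional completed follow-up survey: at the assumed 20 to 44 participants, 20 × 15 = Aus $300 to 44 × 15 = Aus $660.

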### Intervention Condition

The BEAM program is a web-based training program accessible on any internet-enabled device. Each of the 5 modules consists of information, web-based interactive activities, and downloadable resources related to adolescent mental health. In this trial, participants can complete the 5 program modules in any order; however, an initial module is suggested to participants based on their response to the *module recommendation* question in the baseline survey. This question presents participants with a list of 10 topics (such as *signs and symptoms* and *about my role*) that are linked to the learning objectives of each module. Participants are then asked to rate the 3 they are most interested in learning about from 1 (*most interested*) to 3 (*least interested*). The program then recommends that they begin with the module corresponding to their first choice. Each module includes an optional peer coaching activity that asks participants to meet with a colleague from their school to discuss focus questions, practice, and apply program learnings. Participants then submit their responses to the focus questions through the program. The research team then send standardized feedback via email within 3 business days. Participants who do not have another colleague from their school taking part in the trial can either complete the peer coaching themselves, talk to another colleague who is not taking part, or skip the activity, as it is not mandatory. No other program activities are reviewed by the research team. All participants receive access to the program at no cost for 10 weeks, and it is estimated that the full program takes approximately 6.5 hours to complete. Participants can complete the program at their own pace; however, they are recommended to undertake 1 module per fortnight. Given the current COVID-19–related school closures and physical distancing guidelines, participants are encouraged to complete the peer coaching activities via teleconference or phone. Participants will receive fortnightly email reminders to use BEAM and optional SMS reminders. All program use data are collected by the BDI web-based eHealth research platform hosted on the UNSW servers.

### Control Condition

This study uses a waitlist control condition. Participants in the control condition will receive access to the intervention at no cost immediately after they complete the follow-up survey (22 weeks post baseline). If they do not complete the follow-up survey, they will receive access immediately after the survey has closed. They will receive access to the full program whether they have not completed the survey or not.

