### Randomization and Blinding

Cluster randomization at the school level is used to avoid potential contamination and bias effects from other participants, reduce administrative tasks for schools, and enable implementation of the peer-to-peer component of the program. As such, all participants from the same school will be allocated to the same condition and complete the trial at the same time using randomly permuted block randomization with block sizes of 2 and 4. Schools will be assigned to either the intervention or control arm using a 1:1 allocation, stratified by school size (<400 or >400 students) and index of community socioeducational advantage (ICSEA) level (<1000 or >1000) as per a computer-generated randomization schedule. Randomization is conducted by a statistician not involved in the day-to-day running of the trial to avoid influence or bias. The research team will be aware of the allocation once registration is scheduled to begin because they are responsible for providing the link to participants for the intervention or control program study website. Participants will be unaware of which group they are allocated to during registration and baseline. Upon completion of baseline, they will be informed, via email, of their allocation. This is because the intervention participants will receive immediate instructions and access to the program, and the waitlist control participants will be asked to wait for their next survey.

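### Control educators receive BEAM on finishing their own 22-week survey while same-school colleagues may still be answering, which can slightly dilute the follow-up contrasts

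*Protocol article*

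**What the plan says.** Three parts of the protocol article bear on this.

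- **Release of the program to controls (Control Condition).** Completers: "Participants in the control condition will receive access to the intervention at no cost immediately after they complete the follow-up survey". Non-completers: "If they do not complete the follow-up survey, they will receive access immediately after the survey has closed". The Abstract gives the same trigger for the control arm, namely completion of the follow-up assessment.
- **Survey window (Baseline, Posttest, and Follow-Up Assessments).** "The survey is accessible for 7 days, and participants who do not complete it are automatically withdrawn". For the later surveys: "This process is repeated for the 10-week and 22-week assessments".
- **Program content (Intervention Condition).** "Each module includes an optional peer coaching activity that asks participants to meet with a colleague from their school". Modules also carry downloadable resources.

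Randomization and Blinding gives as one purpose of the design: "Cluster randomization at the school level is used to avoid potential contamination and bias effects from other participants". Two further purposes are listed there: less administration for schools, and making the peer component workable.

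**The concern.** Release is triggered person by person, but the unit of randomization is the school and the survey is open for a week. A control educator who answers on the first day has the program at once. Its peer tasks point them to a same-school colleague, and fellow trial participants are the natural partners: the article offers talking to a non-participant as an alternative for those with no colleague in the trial. Those fellow participants are controls who may not have answered yet.

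At stake is the 22-week comparison. Hypotheses states that the confidence effect should be sustained at follow-up, and Statistical Methods names follow-up as the secondary endpoint. If late-answering controls have picked up program content, their ratings move toward the intervention arm and the difference shrinks. The sharing question under Program Impact on Future Behaviors would not detect this, because that block of measures is collected from intervention participants only.

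**Working it through.** **Inputs from the article.** Planned cluster size 5, ICC 0.07, effect 0.50 SD, 80% power, two-sided 5%, attrition 30% (Sample Size). 295 participants completed baseline in 71 schools (Results). Survey window 7 days. Recommended pace one of the 5 modules per fortnight (Intervention Condition).

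**The plan's own figure.** 64 per arm × design effect (1 + 4 × 0.07 = 1.28) = 81.92, rounded to 82. Then 82 / 0.70 = 117.1, stated as 117 per arm, 234 in total, and 234 / 5 = 46.8, so 47 schools. It reproduces, and nothing in this point changes it.

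**Step 1: who could answer after a colleague has access.** Each school has one first responder, so with m responders per school the share answering later is 1 − 1/m. Attrition is assumed to be spread evenly, and control schools are assumed to resemble all schools.

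| Basis | m, all respond | Share | m, 30% lost | Share |
|---|---|---|---|---|
| Planned | 5 | 80% | 3.5 | 71% |
| Observed, 295/71 | 4.15 | 76% | 2.91 | 66% |

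The share counts anyone who answers later, even by minutes. It measures opportunity, not exposure.

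**Step 2: how long the colleague has had the program.** Assume answers are spread evenly over 7 days. With m = 5 the first arrives on average at 7/6 = 1.17 days. The other four average (5 × 3.5 − 1.17)/4 = 4.08 days. The mean gap is 2.9 days; the maximum overlap is 7 days.

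**Step 3: content covered by then.** 2.9/14 = 0.21 of a module; divided by 5 modules, about 4% of the program. A full 7 days gives 0.5 module, or 10%.

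**Step 4: dilution.** Proportional shrinkage of the follow-up difference = share × uptake × gain. Uptake is the proportion of late responders who pick something up. The article gives no figure, so 5-20% is assumed. Gain is the fraction of the full effect obtained, taken as proportional to content covered: 4-10%.

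- All respond: 0.76 × 0.05 × 0.04 = 0.15%, up to 0.80 × 0.20 × 0.10 = 1.6%.
- With 30% attrition: 0.66 × 0.05 × 0.04 = 0.13%, up to 0.71 × 0.20 × 0.10 = 1.4%.

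The more generous line rounds to about 0.2-2%. As an illustration, a 2% dilution takes 0.50 SD to 0.49 SD. With 82 analysed per arm and design effect 1.28, power goes from 80% to 79%.

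**Step 5: which outcomes are open to it.** At 10 weeks no control participant has access, so the primary endpoint is untouched. Helping behaviors are recalled over 2 months, and 2.9 of about 60 days is roughly 5% of that period. Confidence, knowledge and stigma ratings at 22 weeks are not protected by a recall period in this way and are the most exposed.

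**The case against.** The strongest reply is that this does not matter. The primary endpoint is clean. A control's own access starts only after their own survey, so any exposure is second-hand. Peer coaching is optional, and the overlap lasts days. The bias runs toward no difference, so it should not manufacture a benefit. Apart from sustained confidence, the outcome hypothesized at follow-up is helping behavior, which is little affected. All of this stands, and it is why the point is minor.

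A second reply is that immediate access rewards answering, and the article itself names the 22-week wait as an attrition risk. This stands only in part. Non-completers already get the program when the survey closes, so completing buys at most a few days' earlier access, and the follow-up voucher is unaffected.

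Three stronger readings are tempting and not supported:

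- *That the rule undoes the cluster design.* Everyone in a school shares a condition, so contamination between arms within a school remains excluded at 22 weeks. Only a brief overlap within the control arm is left, and avoiding contamination is one of three stated purposes.
- *That the follow-up difference could shrink by up to about 8%.* That takes 0.80 × 0.20 × 0.50: late responders gaining half the full effect second-hand. Even the lower end of such a range, a quarter of the effect, sits badly with a colleague some 4-10% of the way through. The pace is recommended rather than enforced, and the program takes about 6.5 hours, so faster coverage is possible, but the article gives no basis for assuming it.
- *That the overlap reaches about 13 days.* This requires the 22 weeks to run from each person's own baseline completion, as the Design wording could suggest. The assessment procedure describes invitations by wave, repeated at the later time points, which caps the overlap at 7 days.

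**Conclusion.** The point holds as a small, avoidable weakness. The release rule and the 7-day window together let program content reach control educators before they give their 22-week answers, which does not fit the stated aim of avoiding contamination. About 66-71% of control responders have the opportunity. The likely dilution of the follow-up contrasts is about 0.2-2%, toward the null. That size rests on answers spread evenly over the week, gain proportional to content covered at the recommended pace, and an assumed uptake of 5-20%; the article fixes neither gain nor uptake. The primary analysis and the sample size stand. It is worth changing because the correction costs very little, not because the trial's conclusions are at risk.

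**What to change.** Amend Control Condition so that access is released by school: once all control participants at that school have completed the follow-up survey, or once the survey window has closed, whichever comes first. Completers and non-completers then follow one rule, and the Abstract's description of control access should be brought into line. Results describes follow-up as still to be completed, so at that stage the change could still be made.

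The cost is a platform setting and a sentence of text. Early completers wait up to about one extra week after 22 weeks, and the small incentive of immediate access on completion is lost, although the Aus $15 follow-up voucher remains.
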